## Abstract

**Objective:**

The purpose of this double-blind, randomised, controlled trial is to compare allergic outcomes in children following vaccination with acellular pertussis (aP) antigen (standard of care in Australia) given at 2 months of age versus whole cell pertussis (wP) in the infant vaccine schedule.

**Participants:**

Up to 3000 Australian infants 6 to <12 weeks of age born ≥32 weeks gestation.

**Interventions:**

The intervention is a wP containing vaccine as the first scheduled pertussis vaccine dose instead of an aP containing vaccine.

**Outcomes:**

The primary outcome is a binary indicator of history of IgE-mediated food allergy at the age of 12 months confirmed, where necessary, with an oral food challenge before 18 months of age. Secondary outcomes include (1) history of parent-reported clinician-diagnosed new onset of atopic dermatitis by 6 or 12 months of age with a positive skin prick test to any allergen before 12 months of age, (2) geometric mean concentration in pertussis toxin-specific IgG before and 21 to 35 days after a booster dose of aP at 18 months of age, and (3) sensitisation to at least one allergen by 12 months of age.

**Results:**

Operating characteristics of trial decision rules were evaluated by trial simulation. The selected rules for success and futility approximately maintain type I error of 0.05 and achieved power 0.85 for a reduction in the primary outcome from 10% in the control group to 7% in the intervention group.

**Discussion:**

A detailed, prospective statistical analysis plan (SAP) is presented for this Bayesian adaptive design. The plan was written by the trial statistician and details the study design, pre-specified adaptive elements, decision thresholds, statistical methods, and the simulations used to evaluate the operating characteristics of the trial. Application of this SAP will minimise bias and supports transparent and reproducible research.

**Trial registration:**

Australia & New Zealand Clinical Trials Registry, ACTRN12617000065392. Registered on 12 January 2017

**Study protocol:**

10.1136/bmjopen-2020-042838

**Supplementary Information:**

The online version contains supplementary material available at (10.1186/s13063-021-05874-6).

## Introduction

Combination vaccines containing whole-cell pertussis (wP) antigens were phased out from the Australian National Immunisation Program (NIP) between 1997 and 1999 and replaced by vaccines containing less reactogenic acellular pertussis (aP) antigens. In a case-control study of Australian children born during the transition period, those with allergist diagnosed IgE-mediated food allergy were less likely to have received whole-cell vaccine in early infancy than matched population controls [odds ratio 0.77, 95% confidence interval (0.62, 0.95)] [1]. The notions of mechanistic plausibility that support these results are based on the Th_1_/Th_17_ immune-modulating properties of some components of *Bordetella pertussis* within wP formulations, which could promote the development of oral tolerance in children predisposed to maintain Th_2_- biased responses into later infancy [2].

We hypothesise that a single dose of whole-cell vaccine in early infancy is protective against IgE-mediated food allergy in early childhood.

This statistical analysis plan (SAP) provides a priori specification of the decision-making rules and the statistical methods to be used in a prospective clinical trial. The SAP was prepared after data collection had commenced, but prior to any unblinded data analyses. The coordinating principal investigator was responsible for approving the SAP, and it was reviewed and approved by the trial independent data monitoring safety board (DMSB). The SAP is written to be consistent with the CONSORT 2010 Statement and further guidelines and supports transparent and reproducible research.

## Study synopsis

The OPTIMUM trial is a two-armed, prospective, multi-site double-blinded, adaptive, randomised clinical trial designed to assess the effectiveness of a first scheduled dose of wP vaccine for preventing food allergy, compared to the standard aP vaccine in healthy, vaccine-eligible Australian infants aged 6 to <12 weeks born at ≥ 32 weeks gestation in Australia. The trial uses a Bayesian group-sequential design with pre-specified stopping rules informed by predictive probabilities of trial outcomes given the data available at interim analyses.

The protocol defines two stages of the trial. Stage 1 was designed to obtain detailed solicited adverse event data following each primary pertussis vaccine dose, and post-priming immune response data for the first 150 infants only. Stage 2 was designed as a simpler protocol with less intensive follow-up and fewer visits scheduled.

During stage one, 150 participants were enrolled at Perth Children’s Hospital (PCH), Western Australia, between March 2018 and January 2020. Stage 2 will expand the trial to include sites in Sydney and Melbourne randomising up to 3000 participants including the 150 from stage 1. The stage 1 and stage 2 schedules of assessment are available in the previously published protocol [2].

## Interventions

Eligible participants will be randomised to receive a 0.5-mL dose of the WHO-prequalified pentavalent formulation of diptheria-tetanus-pertussis (whole-cell)-hepatitis-B- *Haemophilus influenzae* type b vaccine (DTwP-HB-Hib) (PENTABIO®PT, Bio Frama, study vaccine), or else a hexavalent formulation of DTaP-HB-Hib plus inactivated poliovirus vaccine (IPV) (INFANRIX HEXA®, GlaxoSmithKline, comparator vaccine), as the first dose of the pertussis vaccination schedule between 6 and <12 weeks of age. This is given via intramuscular injection into the anterolateral aspect of the right thigh. Other scheduled 6-week doses are co-administered as per Australia’s National Immunisation Program.

## Study population

### Inclusion criteria

An eligible infant must fulfil all the following: 
Healthy male or female infant aged 6 to <12 weeks old.Born ≥32 weeks gestation.Parent or Legally Accepted Representative (LAR) who has the capacity to understand the parent information sheet and consent form (PISCF) and study related procedures.Parent or LAR is willing and able to give informed consent for participation in the trial.Infant known to be free of significant medical problems as determined by a medical history and clinical examination by a medically qualified investigator.Parent or LAR has access to a telephone.Parent or LAR who is able and willing to comply with the requirements of the protocol in the opinion of an investigator.Parent or LAR is willing to allow other parties involved in the treatment of their child (including general practitioner, medical centre staff, and any other medical professionals the child may be a patient of for the duration of the trial) to be notified of their participation in the trial and for participation in the trial to be recorded within the Australian Immunisation Register (AIR). The parent/LAR is willing to allow the study team to obtain a vaccination history from AIR and/or local provider.Parent or LAR is willing to allow the study team to obtain information from the infant’s doctor, other health care professionals, hospitals, or laboratories concerning the infant’s health from enrolment until 1 month after the 18-month vaccinations.Infant is available for the entire study period.

### Exclusion criteria

The participant may not enter the trial if any of the following apply: 
History of pre-existing parent-reported clinician diagnosed IgE-mediated food allergy.History of parent-reported, clinician-diagnosed pertussis infection.Receipt of any prior vaccine, except for a single birth dose of hepatitis B vaccine within the first 7 days of life (only for visit 1).Contraindication to any routine infant immunisation: history of allergy, including anaphylaxis, to any vaccine or vaccine component.Contraindication to paracetamol.Receipt of investigational vaccines/drugs, other than the vaccines used in the study, since birth or their planned use during the study period, until the final study visit (i.e. at approximately 19 months of age).Receipt, or planned receipt, of any non-routine vaccines within 14 days after the first dose of pertussis containing vaccine.Receipt of more than 2 weeks of immunosuppressants or immune modifying drugs (e.g. prednisolone >0.5 mg/kg/day).Serious chronic illness including severe congenital anomalies affecting heart, brain, and/or lungs.History of any neurologic disorders or seizures.Administration of immunoglobulins and/or any blood products since birth or planned administration during the study period.Planned travel to any region that remains at risk of a poliomyelitis transmission at any time before study visit 8 for stage 1, and for stage 2, before the final phone/electronic contact at approximately 19 months of age.Parents or LAR who plan to move out of the geographical area where the study would be conducted.Any other significant disease or disorder which, in the opinion of the investigator, either may put the participants at risk because of participation in the trial, or may influence the result of the trial, or the participant’s ability to participate in the trial.

### Temporary exclusion criteria for vaccination

Fever (≥38 ^∘^C as determined by axillary assessment) and/or acute disease at the time of recruitment or at any study visit where vaccination will occur as defined by the presence of a moderate or severe illness with or without fever (with the exception of minor illnesses such as diarrhoea, mild upper respiratory infection without fever). In such situations, randomisation or the study visit should be postponed until the participant has recovered.For stage 1 (visits 2, 3, and 7 only), receipt of any vaccination with a licensed vaccine product, including seasonal influenza vaccination or meningococcal vaccination, within the preceding 14 days. In these situations, the study visit should be deferred until 14 days have elapsed.

### Exclusion from per-protocol population

The following criteria will be checked at each visit subsequent to the first visit. If any become applicable during the study, it will not require automatic withdrawal of the participants from the study, but may determine the participant’s evaluability in the per-protocol (PP) analysis. The data would, however, continue to be included in the intention-to-treat (ITT) analysis. 
Use, or planned use, of any investigational or non-registered product (drug or vaccine) other than the study vaccine(s) during the study period, until 1 month after the final study visit (i.e. at approximately 20 months of age).For stage 1 only: Chronic administration (defined as more than 14 days) of immunosuppressants or other immune-modifying drugs during the study period (for corticosteroids, this will mean prednisone ≥0.5 mg/kg/day, or equivalent. Inhaled and topical steroids are allowed).For stage 1 only: 
Administration of a vaccine not foreseen by the study protocol within 14 days after any scheduled vaccine dose.Administration of immunoglobulins and/or any blood products during the study period.Administration of any of the vaccines used in the study outside of the stipulated period.Administration of any live vaccines, those containing tetanus- or diphtheria-related antigens or those that contain bacterial lipo-polysaccharide or other adjuvanted vaccines between study visit 3 and study visit 5.

## Objectives and outcomes

### Primary

The primary objective is to determine whether, compared to the standard strategy of 3 priming doses of aP (aP-only), a mixed wP/aP schedule (first dose of wP followed by doses of aP) protects against the development of IgE-mediated food allergy.

The primary outcome is history of IgE-mediated food allergy at the age of 12 months and confirmed, where necessary, by oral food challenge (OFC) before 18 months. A participant will be considered to have the outcome if there is evidence of sensitisation to a food on skin prick test (SPT), and either: 
Unequivocal IgE-mediated food allergy, defined as (i) a positive oral food challenge, or (ii) history of clinician-diagnosed food anaphylaxis, with symptoms affecting at least 2 of the following: skin, gastrointestinal tract, respiratory tract, and cardiovascular system,Highly probable IgE-mediated food allergy, defined as history of food allergic reaction consistent with PRACTALL criteria [3].

### Secondary

The protocol defines a number of secondary objectives and associated outcomes. These are numbered below.

#### Clinical and mechanistic

Compare the rate of new onset atopic dermatitis in each study group: two binary outcomes will be investigated: 
A history of parent-reported clinician-diagnosed new onset atopic dermatitis by 6 months of age and a positive SPT to any allergen by approximately 12 months of ageA history of parent-reported clinician-diagnosed new onset atopic dermatitis by 12 months of age and a positive SPT to any allergen by approximately 12 months of age.Compare the rate of SPT positivity to common allergens in each study group: two binary outcomes will be investigated: 
A SPT wheals >1mm greater than the negative control to at least one allergen by approximately 12 months of ageA SPT wheals ≥3mm greater than the negative control to at least one allergen by approximately 12 months of age.

#### Stage 1: Atopic immunophenotypic response and vaccine response

3Compare the Th2 immunophenotypic response to tetanus toxoid and egg antigens in infants in each study group: IgE concentrations to the following antigens will be collected at approximately ages 6 (immediately prior to third pertussis-containing vaccine dose) and 7 months (21-35 days after vaccination) using ImmunoCAP total and antigen specific IgE assays (Thermo Fisher Scientific/Phadia, Uppsala, Sweden) during stage 1 only (150 participants): 
Total IgE concentrationIgE concentration to tetanus toxoid vaccine antigenIgE concentration to egg white antigenIgE concentration to whole egg antigen.Assays will be in kU/L per sample. IgE levels ≥0.10 kU/L are considered positive. The total IgE low-range assay can detect concentrations between 0.1 and 100 kU/L. The total IgE high-range assay has range 2 to 5000 kU/L. The specific IgE are reported in the range 0.00 to 100.00 kU/L with results above 100.00 kU/L reported as above this limit.

4Compare vaccine antibody responses in each study group: vaccine antigen-specific IgG concentrations/titres will be measured at approximately ages 6, 7, 18, and 19 months using a multiplex fluorescent bead assay [4, 5], for the following during stage 1 only (150 participants). 
Pertussis toxin (PT)Filamentous haemagglutinin (FHA)Pertactin (PRN)Tetanus toxoid (TT)Polyribosylribitol phosphate (Hib-PRP)13-valent pneumococcal vaccine (serotypes 1, 3, 4, 5, 6A, 6B, 7F, 9V, 14, 18C, 19A, 19F, and 23F)Hepatitis B surface antigen (HBsAg)Diphtheria toxoid (DT)The seropositive thresholds for pertussis antigens are: 
≥5 IU/mL for PT, FHA, and PRNThe seroprotective thresholds other antigens are: 
≥0.1 IU/mL for TT [6] and DT≥10 mIU/mL for HBsAg≥1*μ*g/mL for Hib-PRP [7]≥0.35*μ*g/mL for pneumococcal serotypes [8, 9]For each antigen, we will assess the ratio of the geometric mean titres (GMT) or concentrations (GMC) across study groups at each time point, the fold-rise in concentration from 18 (immediately before boosting with a dose of DTaP with inactivated polio vaccine) to 19 months (21-35 days after vaccination), and proportions of seroprotection or seropositivity. A 4-fold rise or greater will be considered indicative of seroconversion. For pneumococcal IgG responses, the lower limit of quantification ranges from 0.3 to 1.9 ng/mL [10]. For the other antigen-specific IgG, the lower limits of quantification range from 0.01 mIU/mL (DT) to 0.43 mIU/mL (FHA) [5].

#### Stage 2: Vaccine response

5Compare vaccine antibody responses in each study group: vaccine antigen-specific IgG concentrations (PT, FHA, PRN, TT, Hib-PRP, 13-valent pneumococcal, HBsAg, DT) as previously listed for stage (1) will continue to be measured at ages 18 and 19 months in stage 2 up to a maximum of 300 participants enrolled at PCH/TKI unless non-inferiority of wP/aP compared to aP is established earlier.

### Safety and tolerability

To assess the local and systemic adverse reactions (ARs) experienced by participants in each study group after administration of the pertussis containing vaccine doses from the day of vaccination (day 0) until 7 days later (day 6), solicited adverse events and intensity grading will be collected by diary cards for the 7 days after vaccination (for participants in stage 1 vaccinations at 2, 4, 6, and 18 months of age and the first 300 participants in stage 2 enrolled at TKI for vaccinations at 2 and 18 months of age). The following solicited adverse events (AEs) will be collected: 
Axillary temperature (fever ≥38 ^∘^C)IrritabilityRestlessnessVomitingDiarrhoeaAnorexiaDrowsinessInjection site reactions (redness, swelling, induration, and pain).

The definition and intensity grading for fever, diarrhoea, and local reactions (except for immunisation site pain) follows the Brighton Collaboration guidelines [11–15]. For other solicited adverse events, intensity grading scales based on impact on daily activities are used (grade 0 or absent; grade 1 if easily tolerated; grade 2, sufficiently discomforting to interfere with normal everyday activities; and grade 3, if prevents normal everyday activities or requires significant medical intervention).

### Vaccine satisfaction

To assess parental dissatisfaction with vaccination in each group after each scheduled vaccine encounter, the following will be collected: 
Stage 1 infants—Primary caregiver reported satisfaction with the vaccination experience on a 5-point Likert scale (from very satisfactory to very unsatisfactory) on day 7 after vaccination at 2, 4, 6, and 18 months of ageStage 2 infants, first 300 enrolments at TKI—Primary caregiver reported satisfaction with the vaccination experience on a 5-point Likert scale (from very satisfactory to very unsatisfactory) on day 7 after vaccination at 2 and 18 months of age.

## Randomisation

Eligible participants will be randomised in 1:1 allocation to receive the study or comparator vaccine. Randomisation is by computer-generated allocation sequence prepared by the trial statistician [JT] and based on randomly permuted blocks of size 6, 8, or 10, and stratified by study site. The randomisation codes are password-protected and held by the trial statistician.

## Blinding

An electronic copy of the randomisation list is distributed by the study statistician to the unblinded pharmacist for printing and concealment. The randomisation list is concealed from all blinded research staff in a non-transparent envelope until completion of the study. An unblinded pharmacist or research nurse obtains the next contiguous allocation from the concealed list (i.e. the lowest available randomisation number) and prepares the study or comparator vaccine into a clear 1-ml ready-to-administer syringe, labelled with the study participant’s number and their identifiers. The syringes are covered to prevent unblinding. At enrolment, vaccines may be administered by either a blinded, or an unblinded nurse. If unblinded, this nurse has no further involvement in the follow-up of the participant. Parents and all other research staff remain blinded until study completion.

To maintain blinding while ensuring all participants receive at least three priming doses of IPV, a dose of DTaP-IPV (INFANRIX®IPV, GlaxoSmithKline, catch-up vaccine), in lieu of DTaP, is administered to all participants at age 18 months.

The blinding process may be broken under compelling medical or safety circumstances. Code breaks will be authorised by the coordinating principal investigator and will be communicated directly to the parents and/or medical team by the trial statistician.

## Sample size

A maximum sample size of 3000 participants is planned; 150 participants in stage 1 and up to 2850 in stage 2. In accordance with trial simulations of the above design, we estimated the trial would have 85% power to detect a reduction in IgE-mediated food allergy by 12 months of age from 10 to 7% while controlling the probability of a type I error at approximately 5%. This effect size was selected on the basis of consultation with clinical stakeholders.

The sample size for this study is adaptive; therefore, the actual trial sample size may be less than 3000 participants. Based on simulations undertaken for the trial design, the actual sample size is likely to be at least 1000 participants given the expected accrual rates and timing of the first interim analysis. We estimated a 69% probability of stopping early for futility if the null were true, and in the alternative scenario (reduction from 10 to 7% in the primary outcome), we estimated 59% probability of stopping early for expected success.

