#### Stopping rules

Two stopping rules are specified: (1) expected success and (2) futility. At each planned interim analysis *k*=1,2,...,*K*, let $n_{i}^{k}$ denote the number of participants in arm *i* who have reached the primary endpoint by the time of interim *k*. Let $y_{i}^{k}$ denote the number of participants in arm *i* out of $n_{i}^{k}$ who met the primary outcome criteria, and *D*_*k*_ denote the available data. In addition to the participants with observed outcomes at interim *k*, there are $m_{i}^{k}$ participants enrolled in arm *i*, of which some unknown $\tilde w_{i}^{k}$ will have a future response. There are also $l_{i}^{k}$ participants who could still be enrolled into arm *i* (in 1:1 allocation up to maximum sample size) of which some unknown $\tilde z_{i}^{k}$ will have a future response.

Using the prediction model and primary analysis model, the following values are calculated 
$$\begin{aligned} \text{PPoS}_{k}^{0}(q) &= \mathbb E_{\tilde w_{1}^{k},\tilde w_{2}^{k}|y_{1}^{k},y_{2}^{k}}\left[\mathbf{1}_{(q,1]}\left\{\mathbb P\left(\delta<0|y_{1}^{k},y_{2}^{k},\tilde w_{1}^{k},\tilde w_{2}^{k}\right)\right\}\right] \\ \text{PPoS}_{k}^{1}(q) &= \mathbb E_{\tilde w_{1}^{k},\tilde w_{2}^{k},\tilde z_{1}^{k},\tilde z_{2}^{k}|y_{1}^{k},y_{2}^{k}}\left[\!\mathbf{1}_{(q,1]}\left\{\mathbb P\left(\delta<0|y_{1}^{k},y_{2}^{k},\tilde w_{1}^{k},\tilde w_{2}^{k},\tilde z_{1}^{k},\tilde z_{2}^{k}\right)\right\}\right]. \end{aligned} $$

The decision rule used for recommendations at interim analyses (assuming at least some number of participants are still to be enrolled to achieve the maximum sample size) is 
$${}d(D_{k})=\left\{\begin{array}{ll} \text{stop for expected success} & \text{if}\ \text{PPoS}_{k}^{0}(q) > \overline{c}_{k} \\ \text{stop for futility} & \text{if}\ \text{PPoS}_{k}^{1}(q) < \underline{c}_{k} \\ \text{continue to analysis }k+1 &\text{otherwise} \end{array}\right. \quad k=1,...,K $$ where $q=0.95, \overline {c}_{k}=0.95$, and $\underline {c}_{k}=0.05$ for all *k* which were selected based on simulations (see Operating characteristics).

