### Missing data

Reasons for missingness will be summarised. Patterns and predictors of missingness will also be investigated and summarised. Descriptive and summary statistics will generally be based on complete-cases data. The primary analyses will be based on complete-cases. Secondary analyses using multiple imputation for missing responses and covariates will be undertaken to investigate sensitivity of the results.

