## Operating characteristics

The operating characteristics of the OPTIMUM trial were estimated using Monte Carlo methods assuming various scenarios for the data generating process.

The final thresholds were selected informally on the basis of their type I error, type II error, and expected sample size. For example, based on the final row of Fig. 1, tresholds consistent with type I error of approximately 0.05 were identified. These threshold combinations were then assessed for power and expected sample size, noting that many combination options result in similar opearting characteristics. Due to the common use of 0.95 as a one-sided threshold, the value *q*=0.95 was selected.

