### Scenarios

A first interim analysis is scheduled to occur when primary endpoint data is available on 200 subjects. Subsequent interim analyses occur after every additional 200 subjects with available endpoint data until a stopping rule is met, or enrolment is already complete at the maximum sample size of 3,000.

Trial data was generated allowing variations in accrual rate and pattern of accrual, time to primary endpoint, true response probability in the control and treatment arms, and decision thresholds (Table 2).

Accrual was assumed to follow a non-homogeneous Poisson process and we investigated varying the baseline rate and varying the shape of accrual by allowing for slow initial accrual and a ramp-up in the latter stages of the trial. We assumed baseline accrual of 16 per week, and 5 per week (slow accrual is worst case for false positives), and a gradually increasing rate of accrual.

Time to primary outcome was assumed to be uniform between 48 and 72 weeks (mean 60 weeks) post-randomisation.

The probability of food-allergy within the standard aP vaccine strategy, $\theta _{a}^{\star }$, and study wP vaccine strategy, $\theta _{w}^{\star }$, populations investigated were $\theta _{a}^{\star }=0.1$ and $\theta _{w}^{\star }\in \{0.05, 0.06, 0.07, 0.08, 0.09,0.1\}$. Data were generated as Bernoulli random variables using the specified probability with time of enrolment generated from the accrual specification, and time to response generated from the time to outcome specification.

A grid of decision threshold values was investigated across all scenarios. For the final analysis, posterior probability thresholds of *q*∈{0.95,0.955,0.96,0.965,0.97} were investigated. Futility thresholds were fixed across all interim analyses and set to $\underline {c}\in \{0,0.025,0.05,0.075,0.1, 0.2\}$. Expected success thresholds were fixed across all interim analyses and set to $\overline {c}\in \{0.8,0.9,0.925,0.95,0.975,1\}$.

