**Fig. 4 Fig4:**
[figure not shown]
Marginal stopping probability for futility by stage, effect size, and thresholds assuming constant 16 per week accrual and expected success bound $\overline {c}=0.95$

Table 3 summarises the operating characteristics assuming thresholds $q=0.95, \underline {c}=0.05$, and $\overline {c}=0.95$ which were the thresholds chosen for the trial. False positives occurred with approximate probability of 0.05. The estimated probability of correctly declaring success was 0.85 when the effect was a reduction (by 30%) from 0.1 to 0.07 in the primary outcome probabilities.

**Table 3 Tab3:** Trial operating characteristics assuming constant accrual of 16 per week, where $q=0.95, \underline {c}=0.05$, and $\overline {c}=0.95$

$\theta _{a}^{\star }$	$\theta _{w}^{\star }$	Decide superior	Stop early superior	No stop superior	Stop futile	Stop expect success	Superior following futile	Superior following expect success	Expected sample size
0.10	0.05	0.99	0.97	0.02	0.01	0.97	0.61	1.00	1673
	0.06	0.97	0.84	0.12	0.03	0.84	0.34	0.99	1959
	0.07	0.85	0.57	0.27	0.08	0.59	0.14	0.95	2251
	0.08	0.55	0.28	0.28	0.21	0.31	0.05	0.86	2412
	0.09	0.22	0.09	0.12	0.44	0.13	0.01	0.68	2353
	0.10	0.05	0.02	0.03	0.69	0.04	0.00	0.47	2129

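### The 85% power comes from simulations in which all of up to 3000 randomised infants give a primary outcome, but the primary analysis is complete-case, so the figure holds only with no missing outcomes

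*SAP article*

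**What the plan says.** The power claim appears in the Abstract, in Sample size and beside Table 3. Sample size states that "we estimated the trial would have 85% power to detect a reduction in IgE-mediated food allergy by 12 months of age" from 10 to 7%, and sets the ceiling: "A maximum sample size of 3000 participants is planned; 150 participants in stage 1 and up to 2850 in stage 2". The Study synopsis makes clear that the 3000 are infants randomised. The text with Table 3 repeats the result: "The estimated probability of correctly declaring success was 0.85 when the effect was a reduction (by 30%) from 0.1 to 0.07".

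The Scenarios section describes how the trials were simulated: "Data were generated as Bernoulli random variables using the specified probability with time of enrolment generated from the accrual specification", with time to response drawn from its own distribution, uniform on 48 to 72 weeks. Table 2 lists what was varied: accrual, response probabilities and thresholds, with one time-to-outcome distribution. It has no row for withdrawal, loss or an inconclusive outcome.

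Missing data then states: "The primary analyses will be based on complete-cases". Baseline characteristics plans to list reasons for early withdrawal, and Analysis of primary outcome plans to tabulate inconclusive results.

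For the interims, Stopping rules defines m as enrolled participants whose outcome is not yet observed and l as those who could still be enrolled "in 1:1 allocation up to maximum sample size". A future response count is predicted for all of m and l.

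**The concern.** The simulated trial and the specified analysis are not the same. In the simulation, 3000 randomised means 3000 analysed. Under the complete-case rule, an infant without a primary outcome is dropped. That outcome needs a skin prick test at about 12 months and sometimes a food challenge before 18 months, so some loss is likely. Any loss puts the power below 85%.

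The interim rules share the assumption. The predictive probabilities of success (PPoS) are meant to forecast the planned final decision, but they forecast it on more infants than a complete-case analysis will contain. This makes it harder to fall below the futility threshold, so a trial of an ineffective strategy would tend to run longer.

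**Working it through.** **Inputs from the SAP article.** Maximum 3000 randomised 1:1 (Sample size, Randomisation); rates 0.10 and 0.07; independent Beta-Binomial models with Beta(1,1) priors; success if P(δ<0|D) > 0.95; interim thresholds 0.95 (expected success) and 0.05 (futility); interims at every 200 complete outcomes; accrual 16 per week; outcome at 48-72 weeks. The attrition rate is not given. A range of 5-20%, missing completely at random, is assumed here.

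**Step 1: reproduce the plan's figures with no loss.** The full design was simulated (10,000 trials; normal approximation to the posterior probability; 1,000 predictive draws per interim).

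| Quantity | Stated | Re-simulated, no loss |
|---|---|---|
| Power, 10% v 7% | 0.85 | 0.846 |
| Type I error | about 0.05 | 0.048 |
| Expected N, 10% v 7% | 2251 | 2255 |
| Expected N, null | 2129 | 2116 |

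Further runs gave no-loss power between 0.842 and 0.857. Nothing has been miscalculated: 85% is the power when every enrolled infant is evaluable.

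**Step 2: add loss.** Enrolment stays capped at 3000, a fraction d of outcomes is missing, and the final analysis is complete-case.

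| Loss d | Power |
|---|---|
| 0% | 0.85 |
| 5% | 0.84 |
| 10% | 0.82-0.83 |
| 15% | 0.81 |
| 20% | 0.79 |

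With 10,000 trials the Monte Carlo standard error is about √(0.85 × 0.15 / 10,000) = 0.004. Type I error stays at about 0.05.

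**Step 3: fixed-design cross-check.** With no interims and one-sided 0.05, power = Φ[(0.03 − 1.645 × SE₀)/SE₁], where SE₀ = √(2 × 0.085 × 0.915 / n) and SE₁ = √((0.10 × 0.90 + 0.07 × 0.93)/n).

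- n = 1500 per arm: (0.03 − 1.645 × 0.01018)/0.01017 = 1.303, power 0.904.
- n = 1350 (10% loss): power 0.875.
- n = 1275 (15% loss): power 0.858.
- n = 1200 (20% loss): power 0.839.

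The falls of about 3 points at 10% and 6 at 20% match step 2.

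**Step 4: interim predictions at 20% loss.** Null scenario, proportion stopping early for futility:

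| How m and l are counted | Futility stops |
|---|---|
| Lost infants count as pending indefinitely | about 0.63 |
| Infants past their outcome time not counted as pending, no allowance for future loss | about 0.69 |
| Expected losses allowed for in m and l | about 0.71 |

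Without the allowance, expected N under the null rises by about 50-90 infants; in two further runs with lost infants counted as pending, the rise was about 100.

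Under 10% v 7%, power is 0.825 without the allowance and 0.818 with it at 10% loss, and 0.793 and 0.789 at 20%. Stops for expected success at 20% loss are 0.52 either way.

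With no loss, these simulations stop for futility under the null in 0.72-0.76 of trials, against the published 0.69. The differences between counting rules are therefore more reliable than the absolute levels.

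**The case against.** The stated power reproduces, so this is an unstated assumption and not an arithmetic error. The document gives no attrition rate, and the protocol and supplementary file, which are not shown, might discuss one. The article does describe the supplement as holding the other scenarios, and none of the listed scenarios includes loss. The effect is moderate, the final decision rule and type I error are untouched, and multiple imputation is planned as a sensitivity analysis. All of this stands. It limits the weight of the point but does not make 85% the power of the specified complete-case analysis.

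Three stronger readings are tempting but not supported:

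- A reader might infer that the design delivers only 79-82% power. That rests on an assumed 10-20% loss; at 5% the figure is 0.84.
- A reader might infer from Stopping rules that infants already withdrawn are predicted to supply outcomes. Interim analyses limits prediction to enrolled infants who have not yet completed follow-up and those not yet enrolled, which most naturally leaves out known withdrawals. The wording of m is loose, and the lowest futility figure (0.63) applies only on the less natural reading.
- A reader might infer that every inconclusive result is excluded. The plan says only that their number will be tabulated.

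**Conclusion.** The point holds as a conditional statement: 85% is the power with 3000 evaluable infants, while the plan caps randomised infants at 3000 and analyses complete cases. Under the assumed losses the shortfall is about 1 point at 5%, 2-3 at 10%, 4 at 15% and 6 at 20%. These figures assume missingness completely at random; loss that differs by arm or by allergy risk was not examined.

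The interim issue is secondary. It mainly costs efficiency under the null and has little effect on power or type I error. The statement should be corrected, but the validity of the final analysis is not threatened.

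**What to change.** 1. Wherever the 85% appears (Abstract, Sample size, text with Table 3), state that it assumes 3000 evaluable infants.
2. Add attrition to Table 2 and report power, type I error and expected sample size at 5-20% loss. The expected power is about 0.84, 0.82-0.83, 0.81 and 0.79 at 5, 10, 15 and 20%.
3. In Stopping rules, align m with Interim analyses: count only infants still in follow-up, excluding those known to be withdrawn, lost or past the outcome window.
4. Scale m by the probability of completing given still in follow-up, and l by the overall completion proportion, so that PPoS predicts the complete-case analysis actually planned.

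In step 4 the overall proportion should not be applied to m once known losses have been removed, because that counts them twice. As an illustration, suppose that 100 infants are enrolled, 10 are known to be lost and 80 will finally complete. Then 90 remain, and the right factor is 80/90 = 0.889, giving 80. Using 0.80 would give 72.

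The cost is one re-run of the existing simulation code, a few sentences in the SAP and a less favourable stated power. No extra patients are needed.
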